The composite endpoint comprises four pre-specified outcome combinations, addressed as follows: The primary analysis of treatment failure includes three specific scenarios: (i) program non-completion, defined as failure to attend the requisite number of SET sessions, regardless of functional outcome; (ii) functional non-response among program completers, characterized by completion of the program without achieving the MWD threshold at three months (T1); and (iii) revascularization occurring within the three-month follow-up period, irrespective of functional outcome. This approach aligns with the protocol’s objective of identifying patients capable of deriving sufficient benefit from conservative management alone. The rationale for classifying revascularization as treatment failure, even when accompanied by functional improvement, is that such cases indicate the conservative management pathway was not maintained. Sensitivity analysis #6 (Table 3) examines the subset of guideline-concordant revascularization events separately.

The four pre-specified outcome combinations are: (1) functional improvement achieved AND revascularization-free = treatment success; (2) functional improvement not achieved AND revascularization occurred = treatment failure; (3) functional improvement achieved BUT revascularization occurred = classified as treatment failure in the primary analysis; this discordant case type (functional improvement with revascularization) will be specifically examined in sensitivity analysis #6 (Table 3), restricting to guideline-concordant revascularization events only, to assess whether revascularization was guideline-concordant or driven by patient preference; (4) functional improvement not achieved AND revascularization-free = treatment failure. Failure to meet either criterion (b) or the MWD threshold in (a) constitutes treatment failure.

MWD is assessed by a trained physiotherapist blinded to body composition data. Revascularization events are independently adjudicated by a vascular surgeon blinded to body composition data and predictor values, classified as: guideline-concordant (meeting ESVS 2024 criteria for intervention in claudication); patient-preference driven (not meeting objective intervention criteria); or indeterminate. For this study, guideline-concordant revascularization is defined according to ESVS 2024 criteria [4], requiring all three of the following: (a) failure to achieve meaningful functional improvement after an adequate SET trial (≥12 weeks); (b) lifestyle-limiting claudication symptoms refractory to conservative management; and (c) documented hemodynamic deterioration via ABI measurement. Events that do not meet all three criteria are classified as non-concordant or patient-preference driven. Pre-specified sensitivity analyses include composite threshold alternatives (≥40% and ≥60% relative, and ≥100 meters absolute MWD gain) and separate analyses of functional improvement and revascularization outcomes independently.

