## Introduction

Peripheral arterial disease (PAD) affects approximately 236 million individuals aged 25 years and older, with intermittent claudication being its most common symptomatic manifestation [1]. International clinical practice guidelines, including the 2024 American College of Cardiology/American Heart Association (ACC/AHA), 2024 European Society of Cardiology (ESC), and 2024 European Society for Vascular Surgery (ESVS) guidelines, unanimously endorse supervised exercise therapy (SET) as the first-line treatment for intermittent claudication [2–4]. Furthermore, the 2024 ESC and ESVS guidelines specify that revascularization should be deferred until conservative management has been adequately trialed [3, 4]. A Cochrane systematic review demonstrates that exercise significantly enhances maximum walking distance and functional performance compared to no exercise [5]. Additionally, a second Cochrane review confirms the superiority of SET over home-based exercise and walking advice alone [6]. A meta-analysis of 15 randomized controlled trials shows significant improvements in physical health-related quality of life and perceived walking ability with structured exercise programs, although mental health component scores were not significantly affected [7].

Despite these benefits at the population level, individual treatment responses exhibit considerable heterogeneity. In the Invasive Revascularization or Not in Intermittent Claudication (IRONIC) study, 25% of conservatively managed patients ultimately required revascularization over five years, despite achieving comparable long-term outcomes to the revascularization group. This underscores both the tolerability of conservative management and the existence of a subgroup with insufficient response [8]. Real-world SET series report non-completion rates of 40–50% [9]. Conventional clinical predictors — including ankle-brachial index (ABI), age, sex, and disease severity — do not reliably forecast the extent of functional improvement achieved with SET [10]. However, patients with lower baseline walking capacity may derive proportionally greater benefits [10]. Currently, no validated metabolic tool exists to identify, prior to therapy initiation, patients lacking the biological substrate for aerobic adaptation, making them unlikely to benefit from a sustained exercise program.

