### Blinding

This is an observational cohort study without randomization or treatment allocation. The CT analyst performing body composition segmentation is blinded to participant clinical outcomes. The vascular surgeon adjudicating revascularization events is blinded to body composition data and predictor values throughout the follow-up period. Disagreement resolution procedure: In cases where the adjudicating vascular surgeon cannot reach a clear classification (concordant versus non-concordant revascularization), a second independent vascular surgeon reviews all relevant clinical documentation while remaining blinded to body composition data. If disagreement persists after an independent second review, the case is resolved through consensus discussion between both adjudicators; the process and final classification are documented in the study log. Indeterminate cases after consensus are classified as non-concordant for the primary analysis and concordant in a pre-specified sensitivity analysis. Given the observational, non-interventional nature of this study and the absence of experimental treatment allocation, no independent data monitoring committee is established; no interim analyses or stopping rules are pre-specified.

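### Sensitivity analysis #6 cannot examine improved-but-revascularised patients as intended, because a guideline-concordant event requires that improvement failed after at least 12 weeks of SET

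*Protocol article*

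**What the plan says.** All places are in the Protocol article, Materials and methods.

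- **Definition of concordance (Primary outcome).** An event is guideline-concordant only under a rule "requiring all three of the following": the first criterion is "a) failure to achieve meaningful functional improvement after an adequate SET trial (≥12 weeks"), the second is lifestyle-limiting symptoms that persist despite conservative care, and the third is "c) documented hemodynamic deterioration via ABI measurement". Anything else is disposed of thus: "Events that do not meet all three criteria are classified as non-concordant or patient-preference driven".
- **Purpose of #6 (Primary outcome, outcome combination 3; Table 3, row 6).** For patients who improved but were revascularised, "this discordant case type (functional improvement with revascularization) will be specifically examined in sensitivity analysis #6 (Table 3), restricting to guideline-concordant revascularization events only". The stated aim is to learn whether the procedure was concordant or driven by patient preference.
- **Primary composite (Primary outcome).** Failure includes "revascularization occurring within the three-month follow-up period, irrespective of functional outcome". The adjudicated class plays no part.
- **SET section.** The programme runs for 12 weeks.
- **Table 3, row 4.** A mandatory analysis of the functional component with no revascularisation criterion.
- **Blinding.** "Indeterminate cases after consensus are classified as non-concordant for the primary analysis and concordant in a pre-specified sensitivity analysis".

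**The concern.** Improvement is what makes a case discordant, and failure to improve is what makes an event concordant. An analysis restricted to concordant events therefore shuts out the cases it is supposed to look at, and its answer for them is settled by the definition before any data are collected.

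The 12-week minimum also uses up nearly the whole three-month window, so few events of any kind could qualify. The Discussion relies on this adjudication to answer the worry that elective procedures reflect preference rather than failure of conservative care. #6 is the only listed analysis that tries to separate the two kinds of event, and a reader of the final report could take its result as reassurance that it cannot give.

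**Working it through.** The plan gives no figure for #6, so the check is one of logic and timing.

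**1. Logic.** Take success on the walking-distance criterion at three months, revascularisation within the window, and concordance as defined. Assume that meaningful functional improvement in the first criterion is the primary walking-distance threshold, and that programme non-completion is handled the same way in #4 and #6. The article does not say what #6 does with a patient who has a non-concordant event, so both readings are shown.

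| Improved | Revascularised | Concordant | Primary | #6, event no longer counted | #6, patient excluded | #4 |
|---|---|---|---|---|---|---|
| yes | no | – | success | success | success | success |
| yes | yes | no | failure | success | excluded | success |
| yes | yes | yes | cannot arise | – | – | – |
| no | no | – | failure | failure | failure | failure |
| no | yes | no | failure | failure | excluded | failure |
| no | yes | yes | failure | failure | failure | failure |

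The discordant-and-concordant row has no members. Every concordant event falls in a patient who has already failed on function, so it changes nobody's status. On the first reading the #6 column equals the #4 column in every possible row. On the second, every discordant case is removed.

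**2. Timing.** SET lasts 12 × 7 = 84 days. Three months is 90 to 92 days. If SET starts on the day the window opens, the time in which an event can follow 12 weeks of SET and still count is:

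- 90 − 84 = 6 days (6/90 = 6.7%)
- 91 − 84 = 7 days (7/91 = 7.7%)
- 92 − 84 = 8 days (8/92 = 8.7%)

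A delay in starting SET comes straight off this. With a delay of 8 days even the longest window leaves 92 − 84 − 8 = 0 days.

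**3. Indeterminate events.** The Blinding section gives them a class for the primary analysis. There any in-window revascularisation is a failure whatever its class, so the instruction has no effect. The class could matter only in #6, to which the Blinding section does not link it. The Primary outcome section also names an indeterminate class and then sends every event that misses a criterion to one of two other labels, so it is unclear when an event may be indeterminate.

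**The case against.** Several points on the other side are sound.

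- **The composite is not unprotected.** A reader might infer that #6 is the only safeguard against preference-driven procedures. It is not: #4 removes all revascularisations, is mandatory, and must be published whatever the composite shows. No primary estimate, test or sample size uses the concordance label.
- **Empty is too strong.** A reader might infer that no discordant case can ever be concordant. The first criterion is judged before the procedure and the composite at three months, so a patient can fail at week 12, be revascularised and then pass. An indeterminate event may also be counted as concordant. And the definition does not expressly tie meaningful improvement to the walking-distance threshold, although the Discussion presents that threshold as the minimum for a meaningful response. A different reading leaves some room in the logic but none in the timing.
- **Non-concordance during SET may be intended.** The Introduction says guidelines defer revascularisation until conservative care has been tried. That would be a coherent definition; it still does not serve the purpose given to #6.
- **Too few events to model.** A reader might start from the statement that "25% of conservatively managed patients ultimately required revascularization over five years" and infer that #6 cannot be fitted. At constant hazard, which is an assumption, −ln(0.75)/20 = 0.0144 per quarter, a three-month risk of 1.43%, or 1.8 of 128. But #6 re-scores a composite for which the plan expects about 40 failures (128 × 0.78 × 0.40 = 39.9), so revascularisations are not its event count. The Sample size section also says the trial behind that figure was not designed to quantify SET-specific non-response.
- **ABI.** Table 4 has no ABI row, and a reader might infer that the third criterion cannot be assessed. It asks only for documented deterioration, which clinical records may supply. TASC II class is also recorded at baseline without a row in that table.

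What remains is the conflict between the aim of #6 and the definition it depends on.

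**Conclusion.** The point holds in a limited form. As written, #6 cannot separate concordant from preference-driven revascularisation among patients who improved. It essentially duplicates #4 or discards essentially all of the cases of interest, depending on an unstated scoring rule. Criterion (a) can be met in only about 6 to 8 of 90 to 92 days, and in none if SET starts 8 or more days into the window.

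The logical part assumes that meaningful improvement is the primary walking-distance threshold and sets aside the narrow exceptions above. The duplication of #4 further assumes that non-completion is treated alike in both analyses. The timing part needs neither assumption. The primary analysis is untouched. Which clinical criteria for revascularisation are right is not judged here.

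**What to change.** Reconcile the Primary outcome section, Table 3 row 6 and the Blinding section before enrolment opens.

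1. Choose one of two routes. Either base the adjudication label used in #6, for analysis purposes only, on information that does not include the walking-distance outcome; or drop the aim of examining discordant cases through #6 and report them as a descriptive count by adjudicated class.
2. State whether it is intended that any event in the first 12 weeks of SET is non-concordant. If so, say so next to #6.
3. State how #6 scores a patient with a non-concordant event: the event is disregarded and the patient is scored on programme completion and walking distance, or the patient is excluded.
4. In the Blinding section, delete the reference to the primary analysis for indeterminate events, tie the run that counts them as concordant to #6, and make the indeterminate class consistent with the rule for events that miss a criterion.

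The cost is wording in the protocol and the adjudication form, with no new visits, measurements or patients. Enrolment is planned for June 2026; changing adjudication rules once events have been seen would be harder to defend.

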### Secondary and exploratory outcomes

Secondary outcomes, evaluated at baseline (T0) and three months (T1), include: standardized treadmill MWD and PFWD; absolute and relative change in MWD from baseline to T1 (continuous secondary outcomes); 30-second chair stand test repetitions; bilateral handgrip dynamometry (kg); 2-minute walk test distance; and Walking Impairment Questionnaire (WIQ) domain scores. Exploratory outcomes assessed at 6, 12, and 18 months—such as late revascularization, MALE, MACE, and all-cause mortality—are obtained through structured telephone follow-up, medical records review, and registry linkage. Given the anticipated low event counts during extended follow-up in this cohort, exploratory outcomes will be reported descriptively and interpreted as hypothesis-generating only.

### Assessment schedule

The schedule of enrollment, interventions, and assessments is detailed in Table 4.

**Table 4 TB4:** Schedule of enrollment, interventions, and assessments (SPIRIT SoE)

**Assessment**	**Screening (T-1)**	**Baseline (T0)**	**3 months (T1)**	**6, 12, 18 months (T2)**	**Withdrawal**
**Enrollment**	✓				
Eligibility screening	✓				
Informed consent	✓				
**Interventions**					
SET (36 sessions over 12 weeks)		→→→	→ end		
**CT body composition (L3)**					
Existing CTA analysis (T0)		✓			
Exploratory biomarker sampling — all participants (adiponectin, leptin, IL-6; samples stored at T0 and T1; interim assay after the first 40 participants complete follow-up)	✓		✓		
**Primary outcome**					
Composite SET outcome (MWD + revascularization)			✓		
**Secondary outcomes**					
Standardized treadmill MWD and PFWD		✓	✓		✓
30-s chair stand test		✓	✓		
Bilateral handgrip dynamometry		✓	✓		
2-minute walk test		✓	✓		
WIQ domain scores		✓	✓		✓
**Exploratory outcomes**					
MALE, MACE, all-cause mortality				✓	
**Clinical and metabolic data**					
Fasting metabolic panel (glucose, HbA1c, lipids, hsCRP)		✓	✓		
CFS and SPPB		✓	✓		
Adverse events monitoring			→→→	✓	

✓ ═ assessment performed at this time point; → ═ ongoing intervention across this period (arrow span indicates duration); SET delivered over 36 sessions across 12 weeks. Abbreviations: CFS, Clinical Frailty Scale; CT, computed tomography; CTA, computed tomography angiography; HbA1c, glycated haemoglobin; hsCRP, high-sensitivity C-reactive protein; IL-6, interleukin-6; L3, third lumbar vertebral level; MACE, major adverse cardiovascular events; MALE, major adverse limb events; MWD, maximum walking distance; PFWD, pain-free walking distance; SET, supervised exercise therapy; SoE, schedule of enrolment, interventions, and assessments; SPIRIT, Standard Protocol Items: Recommendations for Interventional Trials; SPPB, Short Physical Performance Battery; WIQ, Walking Impairment Questionnaire.

Withdrawal visit procedure: Participants who withdraw from the study prior to the three-month primary outcome assessment are invited to attend a dedicated withdrawal visit within two weeks of discontinuing the SET program. During this visit, standardized treadmill MWD and PFWD are recorded, and the WIQ is administered. These data will be included in the intention-to-treat analysis. Reasons for withdrawal are documented using a structured withdrawal form.

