3	Alternative composite threshold: ≥100 m absolute MWD gain	Tests sensitivity to an absolute rather than relative distance criterion
4	Functional improvement component only (no revascularization criterion)	Isolates the predictive relationship with functional adaptation. Mandatory pre-specified secondary analysis; reported in all primary publications regardless of composite outcome result.
5	Revascularisation-free survival component only	Isolates the predictive relationship with intervention requirement. Mandatory pre-specified secondary analysis; reported in all primary publications regardless of composite outcome result.
6	Restriction to guideline-concordant revascularisation events only	Removes patient-preference-driven events to reduce confounding; specifically examines discordant cases (functional improvement achieved but revascularisation occurred)
7a	Four-predictor model: muscle density, VAT, age, sex (excluding baseline MWD)	Robustness check with an EPV approximately 10; tests stability of primary model estimates when baseline MWD is excluded
7b	Three-predictor model (muscle density, VAT, age; excluding sex)	Robustness check with an EPV approximately 13–14
8	Alternative muscle density threshold: 33 HU	Tests lower threshold sensitivity for myosteatosis classification (Martin et al. [21] value for BMI ≥ 25 kg/m^2^); see also Section 2.6
9	Alternative muscle density threshold: 41 HU [Martin et al. [21], BMI < 25 kg/m^2^ stratum]	Tests higher threshold sensitivity for myosteatosis classification; see Section 2.6
10	Alternative VAT threshold: --20 cm^2^ (110 cm^2^ M; 80 cm^2^ F)**†**	Tests sensitivity to a more conservative VAT threshold
11	Alternative VAT threshold: +20 cm^2^ (150 cm^2^ M; 120 cm^2^ F)**†**	Tests sensitivity to a more stringent VAT threshold
12	Adherent subgroup (≥30/36 sessions completed)	Per-protocol analysis to assess treatment-specific effects
13	30% treatment failure rate scenario (approximately 30 failures)	Reports model performance and power under a more optimistic clinical assumption
14	Expanded confounding model: primary five predictors plus ABI, smoking status, diabetes, Clinical Frailty Scale score, TASC II classification, SMI, SAT	Pre-specified secondary expanded model; EPV approximately 3–4 (acknowledged limitation); designated as robustness sensitivity analysis; tests whether primary predictor associations are independent of additional clinical confounders

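### Walking and questionnaire data from an early withdrawal visit go into the intention-to-treat analysis of outcomes defined at 3 months, with no rule for the difference in timing

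*Protocol article*

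**What the plan says.** The withdrawal procedure stands below Table 4 in the Assessment schedule section. On who is seen: "Participants who withdraw from the study prior to the three-month primary outcome assessment are invited to attend a dedicated withdrawal visit". On when: "within two weeks of discontinuing the SET program". On what is measured: "During this visit, standardized treadmill MWD and PFWD are recorded, and the WIQ is administered". On use: "These data will be included in the intention-to-treat analysis". Table 4 accordingly ticks MWD, PFWD and WIQ in a Withdrawal column that is separate from T1.

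The outcomes are tied to a fixed time. The Primary outcome section sets the MWD threshold at three months (T1). The Secondary and exploratory outcomes section lists "absolute and relative change in MWD from baseline to T1 (continuous secondary outcomes"), and assesses PFWD and WIQ at T0 and T1. Analysis #4 in Table 3 drops the revascularisation criterion and keeps functional improvement alone. It is mandatory and must be reported whatever the composite shows.

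Two other provisions bear on the point. The primary composite counts as failure "program non-completion, defined as failure to attend the requisite number of SET sessions, regardless of functional outcome". The SET section keeps non-adherent participants in the primary analysis.

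**The concern.** SET runs for 12 weeks, so a visit tied to the date of stopping can fall almost anywhere between the first weeks and month 3. No section reconciles that timing with outcomes defined at T1. If the early value enters as the outcome, it stands in for a 3-month value that was never observed. It also stops counting as missing, so it escapes both the multiple imputation and the pattern-mixture and tipping-point analyses. Withdrawers who decline the visit would be imputed to T1, so two people with the same history could be handled in different ways.

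Analysis #4 is the most exposed because its purpose is to isolate functional adaptation. The study's hypotheses are that low muscle density and high visceral fat predict failure, and failure includes non-completion. If the predictors are related to when people stop, they are also related to when walking distance is measured. Timing then becomes a route from predictor to functional result that #4 was meant to exclude. Treating the early value as a known T1 value would also overstate precision.

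**Working it through.** **1. The plan's own attrition figure (Sample size).** 100 evaluable / (1 − 0.22) = 128.2, so the stated 128 reproduces to within rounding. Attrition is 0.22 × 128 = 28.2, about 28 patients. The 22% mixes dropout with protocol non-completion and the visit is by invitation, so about 28 is a ceiling for early values on this figure.

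**2. What the larger percentages measure.** The 40–50% (Introduction, Sample size) and the local audit's 38% (Sample size) are given as programme non-completion or failure. Applied to 128, 38% gives 48.6 (about 49) and 50% gives 64. These would count early values only if every non-completer also left the study and attended the visit.

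**3. Which analyses are exposed.**
- *Primary composite:* non-completion is failure regardless of function, so an early MWD cannot change the result for someone who leaves before attending the required sessions. A narrow gap remains for a participant who attends enough sessions and then withdraws before T1. If the required number is the 30-session adherence cut-off (an assumption), that is at least 30 / 3 = 10 weeks in, so the visit would be close to T1.
- *Analysis #4 and the continuous MWD, PFWD and WIQ outcomes:* these have no such protection.

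**4. Does the text mean imputation only?** The multiple imputation specification lists the composite outcome, the five primary predictors, the expanded-model covariates and the secondary outcomes. It does not name withdrawal-visit values. The Additional measurements section labels the Clinical Frailty Scale and Short Physical Performance Battery as imputation auxiliaries. Withdrawal-visit MWD has no such label. Direct entry as an outcome is therefore the natural reading, though it is implied rather than stated.

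**5. Size of error in #4.** The document gives no trajectory, so every input here is assumed: 12-week gain with mean 100 m and SD 80 m, linear accrual, stopping time uniform over weeks 1–11, visit one week later, test error SD 30 m. The visit then falls on average at week 6 + 1 = 7, which is 5 weeks before week 12. Simulated probability of a gain of at least 50 m among withdrawers:

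| Quantity | Rate | Visit minus true T1 |
|---|---|---|
| At the withdrawal visit | 0.515 | – |
| True T1, half the gain lost after stopping | 0.291 | +0.224 |
| True T1, gain plateaus | 0.514 | about 0 |
| True T1, gain continues at half rate | 0.656 | −0.141 |

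With 22% early values, the cohort error is 0.22 × 0.224 = 0.049 (about 5 points too high) to 0.22 × 0.141 = 0.031 (about 3 points too low), and nil under a plateau.

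**The case against.** The strongest reply is that substitution for T1 is never stated. The sentence does not name #4 or the continuous outcomes, Table 4 keeps Withdrawal apart from T1, and use within the imputation would fit the words. An analysis plan not shown here may settle it. That stands as far as it goes: the carry-forward is inferred. But the protocol does state a rule for these data, and that rule as written points to direct use, for the reasons in step 4 of the working.

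A reader might infer that 38–50% of patients would carry an early value. The documents do not support this. Those are rates of programme non-completion or failure, whereas the withdrawal visit is for people who leave the study. Non-adherers are retained, and nothing removes them from the T1 test. For the same reason, a reader might infer that anyone who merely stops SET is tested early instead of at T1. The reference to stopping SET sets the date of the visit, not who attends it.

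A reader might also infer that the primary result is biased. The non-completion rule largely prevents that.

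Finally, the error sizes rest on assumed inputs, change sign between scenarios and vanish under a plateau. They concern a response rate, whereas the study's target is predictor associations, and no bias in an odds ratio or correlation has been computed. All of that stands. The link between predictors and measurement time is a risk that follows from the study's own hypotheses, not a demonstrated bias.

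**Conclusion.** The point holds for analysis #4 and for the continuous MWD, PFWD and WIQ outcomes. The protocol puts off-schedule measurements into analyses of outcomes defined at T1 and gives no rule for the difference in time. On the plan's own attrition, at most about 28 of 128 patients are affected, fewer if some decline the visit, and late withdrawers contribute little error. The illustrated cohort-level error in the 50 m response rate runs from about 5 points too high to 3 points too low. It depends wholly on the assumed trajectories, and its direction cannot be known in advance. This is a moderate point about secondary analyses. It is worth settling because #4 must be reported in every primary publication.

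**What to change.** Replace the inclusion sentence in the withdrawal visit procedure with a statement of four things:

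- Analysis #4 and the T0-to-T1 outcomes use T1 measurements only.
- Participants who stop SET but remain in the study are tested at T1, as Table 4 already schedules.
- Withdrawal-visit MWD, PFWD and WIQ, with time since T0, enter only as auxiliary variables in the imputation model or in a labelled sensitivity analysis.
- The number and timing of withdrawal-visit measurements are reported.

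The missing T1 values then fall under the planned imputation and tipping-point analyses. The cost is a change of wording and a few auxiliary variables, with no visit beyond those in Table 4. Enrolment is planned to begin in June 2026, so the wording is best settled before then. The downside is slightly wider intervals for #4 and the change outcomes.
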